## Abstract

**Background:**

Patellar instability is a common and understudied condition that disproportionally affects athletes and military personnel. The rate of post-traumatic osteoarthritis that develops following a patellar dislocation can be up to 50% of individuals 5–15 years after injury. Conservative treatment is the standard of care for patellar instability however, there are no evidence-informed rehabilitation guidelines in the scientific literature. The purpose of this study is to assess the effectiveness of blood-flow restriction training (BFRT) for patellar instability. Our hypotheses are that this strategy will improve patient-reported outcomes and accelerate restoration of symmetric strength and knee biomechanics necessary to safely return to activity.

**Methods/design:**

This is a parallel-group, superiority, randomized, double-blinded, placebo-controlled clinical trial at the University of Kentucky, sports medicine clinic that aims to recruit 78 patients with acute patellar dislocations randomly allocated into two groups: (1) sham BFRT and (2) BFRT. Both groups will receive the current standard of care physical therapy 3 times per week for up to 9 weeks. Physical therapy sessions will consist of typical standard of care treatment followed by BFRT or sham BFRT. Primary outcomes include the Norwich Patellar Instability Scale, quadriceps strength, and imaging and biochemical biomarkers of cartilage degradation.

**Discussion:**

The current standard of care for non-operative treatment of patellar instability is highly variable does not adequately address the mechanisms necessary to restore lower extremity function and protect the long-term health of articular cartilage following injury. This proposed novel intervention strategy uses an easily implementable therapy to evaluate if BFRT significantly improves patient-reported outcomes, function, and joint health over the first year of recovery.

**Trial registration:**

Blood Flow Restriction Training, Aspiration, and Intraarticular Normal Saline (BRAINS) NCT04554212. Registered on 18 September 2020.

## Background

Patellar dislocations are a common and understudied condition that disproportionally affects athletes and military personnel [1]. The rate of having a patellar dislocation is greater than having an anterior cruciate ligament (ACL) tear in this population [1]. Regardless of intervention, 30% to 50% of those who sustain a primary dislocation experience continued pain and the sensation of instability [2]. A significant long-term concern is the rate of post-traumatic osteoarthritis that develops following a patellar dislocation which can be up to 50% of individuals within 5–15 years after injury [3]. Nonoperative treatment is currently the standard of care following most first-time dislocations; however, 31% of patellar instability patients treated conservatively suffer a re-dislocation [4]. A single patellar dislocation increases the lifetime risk of post-traumatic osteoarthritis (PTOA) and recurrent dislocations markedly increase this risk [3, 5]. Therefore, there is an urgent need to minimize the incidents of recurrent patellar dislocations and PTOA sequela which safely allows an earlier return to sport or work while also limiting long-term functional impairments and reduced quality of life.

While nonoperative treatment is most commonly employed for patellar instability, specific evidence-informed rehabilitation guidelines are sparse [4]. One modality that could potentially improve treatment for those with patellar instability is blood flow restriction training (BFRT). BFRT involves the use of an inflatable cuff applied to the thigh to slow arterial blood flow and eliminate venous return as subjects exercise with a relatively low resistance. It is thought that the increased metabolic stress and mechanical tension during BFRT act to stimulate various metabolic pathways leading to muscle hypertrophy [6–8]. There is evidence supporting the premise that BFRT will result in improved quadriceps and hip strength without the need for high-intensity resistance exercise [9–11]. Due to the nature of patellar instability, patients may not tolerate high-intensity quadriceps exercises early in the rehabilitation process thus delaying the recovery of strength. BFRT may allow them to receive the same training benefits as if they were training under high loads. Achieving greater muscle strength earlier after injury may result in improved lower extremity biomechanics, improved functional capacity, and an accelerated recovery.

The purpose of this double-blind randomized clinical trial is to assess whether BFRT in addition to standard physical therapy will improve patient-reported outcomes and accelerate return to work or sport through the earlier restoration of symmetric strength and knee biomechanics, and reduce early cartilage degradation for those with patellar instability.

## Methods/design

### Aims

The overarching rationale is that BFRT will expedite the return to work or sports, minimize muscle impairment, and ultimately slow cartilage degradation over the first year following patellar dislocation. This strategy will improve patient-reported outcomes and accelerate restoration of symmetric strength and knee biomechanics necessary to safely return to activity. We will test the following specific aims:

*AIM 1*: Determine if BFRT improves patient-reported outcomes and lessens the time to return to work or sport following patellar instability.

*Hypothesis:* BFRT will result in significantly improved responses on the patient-reported Norwich Patella Instability, visual analog scale (VAS) for Pain, Cincinnati Occupational Rating Scale, Tegner activity scores, and an earlier return to work and/or sport.

*AIM 2:* Assess whether BFRT results in more symmetric quadriceps strength and knee biomechanics following patellar instability.

*Hypothesis:* BFRT will result in improved quadriceps strength and knee biomechanics (knee moments and excursions).

*AIM 3:* Compare progressive changes in cartilage degradation, muscle architecture, and inflammatory profiles between those treated with or without BFRT over the first 2 years.

*Hypothesis:* BFRT will reduce degradative changes on Magnetic Resonance Imaging (MRI) as well as serum and urinary biomarkers of inflammation and cartilage degradation.

### Participants

Participants will be males and females recruited from the University of Kentucky Sports Medicine Clinic. A sample of 78 patients with patellar instability will be recruited. Potential study participants will be identified by members of the research team during regularly scheduled office visits with 6 physicians at the UK Orthopaedic and Sports Medicine Center. After being identified as a potential study participant, the patient will meet with a research assistant. Provided that the patient meets all inclusion and exclusion criteria, a clinical research coordinator will begin the process to obtain informed consent. Before enrollment, each subject will provide written informed consent. An American Board of Family Medicine-certified physician with a Certificate of Added Qualifications in Sports Medicine, aboard-certified orthopedic surgeon, or a licensed physical therapist will make the diagnosis of patellar instability utilizing the following criteria: patients’ report of at least one episode of patellar instability within the past 3 months, a positive patellar apprehension test during clinical examination, and no evidence on MRI or x-ray of loose body formation or osteochondral defects, avulsion, or osteochondral defect that would require the need for surgical intervention (Table 1).

**Table 1 Tab1:** Inclusion and exclusion criteria for the BRAINS clinical trial for patients with patellar instability

Inclusion criteria	
Diagnosis of traumatic patellar dislocation (either primary or recurrent) determined by an American Board of Family Medicine-certified physician with a Certificate of Added Qualifications in Sports Medicine, a board-certified orthopedic surgeon, or a licensed physical therapist utilizing clinical examination, radiographic imaging, and patients’ reports of instability	
Age 14 to 40 years	
Skeletally mature with closed growth plates visualized by radiograph	
A score of 80 or more on the Sports Activity Scale, which corresponds to participating in “running, twisting, turning (tennis, racquetball, handball, ice hockey, field hockey, skiing, wrestling)” at least 1–3 times per week	
Desire to resume pre-injury activity level	
Exclusion criteria	
Concomitant osteochondral lesion requiring surgical fixation	
Radiographic evidence of osteoarthritis (≥ Kellgren-Lawrence Grade 2)	
Previous ipsilateral or contralateral knee surgery	
Most recent instability event more than 3 months before enrollment	
History of intra-articular injection into either knee within 3 months	
History of any inflammatory disorder	
Body mass index > 35 kg/m^2^	
Diabetes or uncontrolled hypertension	
Varicose veins or a history of personal or immediate family history (parental or sibling) of deep vein thrombosis	

### Design

This is a parallel-group, superiority, randomized, double-blinded, placebo-controlled clinical trial that begins in the winter of 2022 and will continue for 4 years. This study will take place at the University of Kentucky, and has been approved by the University of Kentucky IRB (IRB #56541, ClinicalTrials.gov Identifier: NCT04554212). Any changes to the protocol will be first reviewed by the local IRB and then communicated to the entire study team upon approval.

### Randomization, group allocation, and blinding

Randomization: Following informed consent and after successfully being screened into the study based on exam findings, subjects will be randomized to one of two groups. The randomization schedule will be made a predesignated unblinded study team member that will not be involved in data collection or analysis. Using a random number generator, allocation of to either the BFRT or sham BFRT group will be by permutated random block size, ensuring that approximately equal numbers of subjects will be treated with drug or placebo in the unlikely event that the study will need to be terminated prematurely. Should a subject discontinue the study for any reason prior to the final follow-up visit, then the collected data will be evaluated but not included in the analysis and a replacement subject will be enrolled in the study. As such, the randomization schedule will be prepared for 100 potential participants despite having a target enrollment of 78 participants to ensure adequate power.

Blinding: The team member that prepared the randomization schedule will meet with the pre-specified unblinded study personnel prior to the site initiation visit. The unblinded personnel will then prepare sealed envelopes that contain each subject’s group assignment. All assessments and data analyses will be performed by a separate individual to the person applying the BFRT unit to ensure blinding. The study statistician will generate a randomization plan using SAS or R to assign subjects to groups. Randomization will occur by sex and be in sets of 2 subjects to ensure adequate distribution of all groups across the collection period. Patients will be randomized into one of the two following treatment groups:
Standard of care physical therapy + sham BFRTStandard of care physical therapy + BFRT

Should an investigator become inadvertently unblinded, the medical officer and principal investigator will determine the extent of the unblinding and potential ramifications. If necessary, the investigator’s role may need to be altered to only include tasks affiliated with unblinded personnel. Should a patient become inadvertently unblinded, that patient’s data will continue to be collected for safety purposes; however, the data will not be used for the final analyses and a replacement subject will be enrolled. Unblinding of a subject(s) group assignment will be documented and will include an explanation of why the study intervention was unblinded. Following data lock, group assignment can be unblinded and the unblinded information can be sent to the study participants at the discretion of the principal investigator.

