### Statistical methods

The primary outcome variable for Aim 1 is the Norwich Patellar Instability Scale. Utilizing the standard deviation of 18.6 points from our pilot results, a sample size of 34 subjects per group will be adequately powered (80%) to detect a moderate effect size between groups difference (13 points difference, effect size = 0.7). To protect against up to 15% of subjects being lost to follow-up, an additional 5 subjects will be enrolled per group (39 subjects per group; 78 total). Based on our previous pilot work, a sample size of 34 patients per group will also be more than 80% powered to detect group differences in the primary outcome variables for both Aim 2 (quadriceps strength and knee biomechanics) and Aim 3 (T1ρ relaxation time).

Since all endpoints are quantitative and longitudinal data is collected, repeated measures analysis of covariance (ANCOVAs) will be used to assess differences in scales across the two treatment groups (BFRT vs. sham BFRT). The repeated measures ANCOVAs will adjust for demographic covariates (e.g., age, sex, and race) as well as look for differences across any other potential confounders (such as first-time vs. repeated instability events). Assumptions such as normality and constant variance will be assessed, and remedial measures will be employed as needed. In addition, interaction effects and/or variable transformations will be explored appropriately. In the case that endpoints are related, multivariate analysis of covariance (MANCOVAs) may be used to consider those that naturally group themselves.

All analyses will be performed with a significance level of 0.05, and appropriate multiple comparisons adjustments will be performed as needed. Categorical variables will be described with counts and percentages and analyzed using appropriate statistical methods, such as hypothesis tests or logistic regression models.

For both primary and secondary analyses, in the case of participants that violate group allocation or do not attend a minimum of 80% of the prescribed physical therapy sessions, we will perform intention-to-treat and per protocol analyses. We will not employ imputation methods in the case of missing data. No interim or other subgroup analyses will be performed.

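### Randomised participants who leave the study or become unblinded are excluded from the analysis and replaced, which conflicts with the stated intention-to-treat analysis and duplicates the 15% loss allowance

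*Protocol article*

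**What the plan says.** Three parts of the Protocol article bear on who is analysed.

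- **Randomization, group allocation, and blinding (discontinuation).** The trigger is wide: "Should a subject discontinue the study for any reason prior to the final follow-up visit". The consequence for that person is exclusion and substitution: "then the collected data will be evaluated but not included in the analysis and a replacement subject will be enrolled in the study". The schedule is enlarged to match: "the randomization schedule will be prepared for 100 potential participants despite having a target enrollment of 78 participants to ensure adequate power".
- **Same section (unblinding).** Data on a patient who is inadvertently unblinded are still gathered for safety, but "the data will not be used for the final analyses and a replacement subject will be enrolled".
- **Statistical methods.** The sentence on analysis populations applies to every primary or secondary endpoint and is addressed to non-adherence: "in the case of participants that violate group allocation or do not attend a minimum of 80% of the prescribed physical therapy sessions". Its promise for such cases is that "we will perform intention-to-treat and per protocol analyses". The sample size already carries a loss allowance: "To protect against up to 15% of subjects being lost to follow-up, an additional 5 subjects will be enrolled per group". On missing values: "We will not employ imputation methods in the case of missing data". The confidentiality paragraph that closes this section says that data gathered up to withdrawal are kept.

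Nowhere are discontinued or unblinded participants returned to an efficacy analysis.

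**The concern.** An intention-to-treat analysis takes everyone randomised, in the arm to which they were allocated. The exclusion rules remove people because of something that happened after randomisation, at any time up to 12 months. The two instructions are compatible only if nobody leaves and nobody is unblinded, and the plan itself expects up to 15% loss.

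Three things are at stake. First, the comparison becomes one among completers, which randomisation no longer protects if leaving differs between arms in frequency or in reason. That is plausible here, because the arms differ in cuff pressure and discomfort is recorded for each exercise, but the document does not quantify it. Second, valid repeated measurements are set aside. Third, replacement and the 15% inflation both answer the same loss, so it is unclear whether 78 counts people randomised or people completing.

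**Working it through.** **Inputs from Statistical methods:** SD 18.6, target difference 13 points, 80% power, 34 per group, 15% loss, 39 per group (78 total), alpha 0.05 (two-sided assumed). **From Randomization, group allocation, and blinding:** a schedule of 100. **From Outcome measures:** Norwich scale at enrolment, 4 weeks, 9 weeks, 6 months and 12 months.

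**1. The plan's own sample size.** Effect size = 13/18.6 = 0.70. A two-sample t-test needs 33.1 per group, rounded up to 34, where power is 81.0%. Inflation gives 34/0.85 = 40 per group against the stated 39, a difference of two patients in total. The sample size reproduces and is not the fault.

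**2. What is left out.** Someone who leaves between the 6-month and 12-month visits has up to four Norwich assessments: one at enrolment and three afterwards. None enters the analysis.

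**3. Loss covered twice.**
- Replacing until 39 per arm complete: t-test power = 86.2%, against the stated 80%.
- Number randomised to reach 78 completers at 15% loss: 78/0.85 = 91.8, about 92. Excluded: 92 − 78 = 14.
- If all 100 places were used: 22/100 = 22% of those randomised would be outside the analysis.
- Without replacement: 39 × 0.85 = 33.15 per arm with final data. Power is 79.8% at 33 and 81.0% at 34.

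**4. Illustrative bias with no true effect.** Assume that discontinuers in both arms would score g SDs worse than completers, with dropout d1 and d0.
- Spurious difference among completers: b = (d1 − d0) × g × 18.6.
- SE = 18.6 × √(2/39) = 4.21.
- Two-sided type I error = Φ(−1.96 − b/SE) + 1 − Φ(1.96 − b/SE).

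| Dropout by arm | g | b (points) | Type I error |
|---|---|---|---|
| 15% v 15% | 0.5 or 1.0 | 0 | 5.0% |
| 20% v 10% | 0.5 | 0.93 | 5.6% |
| 20% v 10% | 1.0 | 1.86 | 7.3% |
| 25% v 5% | 0.5 | 1.86 | 7.3% |
| 25% v 5% | 1.0 | 3.72 | 14.3% |

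The arm that loses more of its poorly recovering participants looks better than it is. The largest b in the table is 3.72/13 = 29% of the target difference. The dropout rates and g are assumptions; the document gives neither.

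**The case against.** The strongest defence is that the exclusion applies to leaving the study, not to stopping treatment. A participant who gives up the cuff, attends too few sessions or receives the wrong allocation, but comes to the 12-month visit, remains in the analysis. The intention-to-treat sentence is written for those cases, and an as-randomised analysis of them can be run. This stands, and it limits the point: what is blocked is an intention-to-treat analysis of everyone randomised.

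A reader might go further in four ways that the document does not support.

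- **That the data are destroyed.** They are to be evaluated and kept, and are only left out of the analysis. This makes the repair easy.
- **That re-dislocation drives withdrawal.** The Background gives 31% re-dislocation under conservative treatment, with no time frame and no link to leaving the study. No rule makes re-dislocation, surgery or cuff intolerance a ground for withdrawal.
- **That bias is certain.** Equal dropout for equal reasons produces none.
- **That replacement itself biases the comparison.** A replacement takes a further place on the randomisation schedule. The bias risk comes from excluding people already randomised; the case against replacement is redundancy with the loss allowance.

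Nor does ruling out imputation justify the exclusion. A likelihood-based repeated-measures model uses the visits that exist without filling in the others. The exact model may properly sit in an analysis plan not shown here, but the protocol fixes the analysis set, and fixes it in conflict with itself.

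**Conclusion.** The conflict is real and should be corrected before analysis, because the rule decides who counts for every endpoint. As written, any discontinuation or unblinding reduces the promised intention-to-treat analysis to an as-randomised analysis of completers. At the plan's own 15% loss, that means about 14 of 92 randomised participants left out, while the analysed number gives more power (about 86%) than was asked for.

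The effect on the result cannot be fixed from the document. Under the stated assumptions type I error runs from 5%, with no differential loss, to about 14% at 25% versus 5% dropout with discontinuers a full SD worse. The upper end is an illustration and not a forecast.

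**What to change.** In Randomization, group allocation, and blinding:

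- Delete the exclusion of participants who discontinue and the parallel exclusion of unblinded patients. Correcting only the first would still block an analysis of all randomised participants.
- Delete the replacement rule and its 100-place rationale, since the 15% allowance already serves that purpose.
- State that participants who stop treatment are asked to continue their assessment visits to 12 months, where consent allows.

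In Statistical methods:

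- Define the primary intention-to-treat analysis as all randomised participants, in their allocated arm, with every collected visit, for example by a likelihood-based repeated-measures model. This is consistent with using no imputation. It reduces attrition bias when loss is explained by observed data, but does not abolish it, so reasons for leaving should be reported by arm.
- Keep completers-only and per-protocol analyses as supportive.

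The cost is wording. Planned enrolment stays at 78: about 33 per arm with final data gives roughly 80% power, before counting what discontinuers' earlier visits add. At 15% loss it also avoids about 92 − 78 = 14 further enrolments.

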### Blood flow restriction training

Two brands of blood flow restriction units will be used (brand names not included in this text to avoid the potential for subjects to become unblinded). Subjects will be split into groups as previously described where brand 1 will be used as sham BFRT and the intervention group will use brand 2. All quadriceps-focused exercises will be performed with the bands inflated. As directed by the manufacturer’s instructions, the bands will be placed on the proximal thigh as close to the femoroacetabular joint as possible (Fig. 1). Limb arterial occlusion pressure will be constantly monitored and adjusted by the unit to maintain the desired occlusion pressure throughout the duration of exercise. Consistent with our current trial assessing the efficacy of BFRT for ACL reconstruction patients (NCT03364647), participants in all groups will perform the same exercises with an emphasis on quadriceps and hip strengthening, and for those randomized to the active BFRT groups, each BFRT session will last approximately 20 min [12]. All subjects will attend 3 visits per week for 8 weeks divided in to 4 phases.

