**Fig. 1 Fig1:**
[figure not shown]
Blood flow restriction training cuff placement. The BFRT band is applied to the upper thigh of the subject’s leg. Pressure is continuously regulated by the controller unit during training

The active BFRT group will have the arterial blood flow occlusion pressure set per manufacturer instructions to achieve the desired limb occlusion pressure (LOP), whereas the sham BFRT group will have restriction pressure set at a sub-clinical level of occlusion. Occlusion personalized tourniquet pressure (PTP) will be reassessed each visit by rechecking the LOP. Each subject will perform a block of 4–5 quadriceps and hip-focused exercises each lasting approximately 5 min for a total of 20 min (exercises: seated single leg press, seated single leg knee extension, single leg forward step-ups progressed to forward step downs when tolerated, and resisted double leg squats). Exercise intensity will be adjusted between groups to accommodate the achievement of volitional fatigue and an acceptable sensation of discomfort during exercise. Cuffs will be deflated for a minimum of 1 min between exercises. The quadriceps and hip strengthening exercises with the cuff donned will be performed at the end of the rehabilitation session with the intention of reducing the impact of fatiguing the muscles for the standard physical therapy portion of the treatment session.

For all subjects, rating of perceived discomfort and rating of perceived effort will be recorded from separate 11-point Likert-type scale (0 no discomfort or effort to 10 maximal discomfort or effort) for each BFRT exercise. Emphasis will be placed on distinguishing between effort (the amount of physical energy being given to the exercise) and discomfort (the physiological and unpleasant sensations associated with the exercise), with the goal of maximizing effort. All exercises should be challenging and/or hard to perform; however, subjects need to maintain proper form, as determined by the treating physical therapist, to ensure appropriate quadriceps engagement.

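### Dropping and replacing inadvertently unblinded patients is a post-randomisation exclusion that can bias the comparison and does not fit the promised intention-to-treat analysis

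*Protocol article*

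**What the plan says.** The rule is in the protocol article under Randomization, group allocation, and blinding. It begins "Should a patient become inadvertently unblinded, that patient’s data will continue to be collected for safety purposes" and goes on to say that "the data will not be used for the final analyses and a replacement subject will be enrolled". The article also requires each unblinding to be documented with its reason. It gives no expected rate of unblinding and does not define when a patient counts as unblinded.

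The same section treats patients who discontinue in the same way: "the collected data will be evaluated but not included in the analysis and a replacement subject will be enrolled in the study". To make room for replacements, "the randomization schedule will be prepared for 100 potential participants despite having a target enrollment of 78 participants".

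Two statements under Blood flow restriction training describe differences between the arms that a patient might notice. On the device, "brand 1 will be used as sham BFRT and the intervention group will use brand 2", with "brand names not included in this text to avoid the potential for subjects to become unblinded". On pressure, "the sham BFRT group will have restriction pressure set at a sub-clinical level of occlusion".

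Under Statistical methods, the article says that "we will perform intention-to-treat and per protocol analyses" where participants depart from their allocation or attend fewer than 80% of sessions. Unblinding is not among these triggers, and imputation is ruled out.

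**The concern.** Randomisation makes the arms comparable as randomised. A rule that takes patients out because of a later event keeps that comparability only if the event is unrelated to arm and outcome. Unblinding may not meet that condition here, since both the device and the cuff pressure differ by arm. The primary outcome for Aim 1, the Norwich Patellar Instability Scale, is patient-reported.

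Enrolling a replacement brings the count back to target, but the replacement does not stand in for the kind of patient who was removed. Nor does deletion repair the blinding problem. Knowledge of the arm may affect a patient's reported score, but removing that patient swaps a possible reporting bias for a possible selection bias. The article offers no analysis in which these patients are retained.

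**Working it through.** **Inputs from Statistical methods:** SD 18.6 points, target difference 13 points, 34 per group for 80% power, 39 per group enrolled, significance level 0.05 (two-sided assumed, as sidedness is not stated).

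**Reproducing the plan's figure.** n per group = 2 × (1.96 + 0.84)² × 18.6² / 13², which rounds up to 33. A two-sample t test gives 33.1, rounded up to 34. This matches the stated 34. Power at 34 per group is 82% (normal approximation) or 81% (t test).

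**Are the exclusions needed for power?** With all 39 per group analysed, power is 87% (normal) or 86% (t test). Keeping unblinded patients in the analysis therefore needs no larger sample.

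**Size of a possible bias.** The article gives no unblinding rate, so the next inputs are assumptions:
- p = share of one arm excluded, with none excluded from the other: 15%
- D = mean difference in Norwich points between excluded and retained patients in that arm: 10 to 20
- replacements come from the same population under the same rule, so 39 per group are analysed

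Bias = p × D:
- 0.15 × 10 = 1.5 points; 1.5/13 = 12% of the target
- 0.15 × 20 = 3.0 points; 3.0/13 = 23% of the target

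Standard error of the difference = 18.6 × √(2/39) = 4.21 points.

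Type I error with no true effect = Φ(−1.96 + bias/4.21) + Φ(−1.96 − bias/4.21):

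| Bias (points) | Bias / SE | Tail towards the bias | Other tail | Two-sided |
|---|---|---|---|---|
| 0 | 0 | 2.5% | 2.5% | 5.0% |
| 1.5 | 0.36 | 5.4% | 1.0% | 6.5% |
| 3.0 | 0.71 | 10.6% | 0.4% | 11.0% |

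A wider range, with D in SD units: 5% excluded and D = 0.5 SD gives 0.5 points and 5.1%; 20% excluded and D = 1 SD gives 3.7 points and 14.3%.

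**Direction.** The two-sided figure hides which arm gains. If the excluded patients are sham patients who are doing poorly, the retained sham mean looks better and the BFRT effect is understated. With a 3-point bias, a true 13-point difference appears as 10 points. Power at 39 per group falls from 87% to 66%, because 10/4.21 = 2.37 and Φ(2.37 − 1.96) = 0.66. Under no true effect, false claims in favour of BFRT then fall from 2.5% to about 0.4%. If poorly responding BFRT patients are the ones excluded, the error runs the other way and favours BFRT.

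**The case against.** The strongest reply is that the rule may touch few patients and do no harm. Much of that stands, and it limits what can be claimed.

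- **Link to arm.** A reader might infer that the exclusion is tied to treatment arm and so does bias the result. The article does not say that unblinding differs by arm. The different brands and pressures make it plausible, no more. If exclusion is unrelated to arm and outcome, the bias is zero.
- **Guessing.** A reader might infer that patients who guess their arm from discomfort or lack of benefit are dropped. The text speaks of inadvertent unblinding that is documented with a reason, which may mean only disclosure of the assignment, such as a staff slip. The article does not settle which meaning applies, so a response-driven exclusion cannot be asserted.
- **Intention-to-treat.** A reader might see a direct contradiction. Statistical methods ties its two analyses to departures from allocation and low attendance, and does not mention unblinding. The conflict is one of principle: an analysis that leaves out randomised patients by rule is not intention-to-treat, so the two sections need to be reconciled.
- **Device masking.** Withholding the brand names is a safeguard. The article does not say that the units are unmasked, and that operational detail may sit in the full protocol. It is not part of this point.
- **Size.** The 11% figure is the upper end of an assumed range, and its 20-point difference exceeds one SD (18.6).

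The reply does not remove the rule. The article itself fixes who leaves the final analyses, so this is not a detail left to an analysis plan, and nothing elsewhere brings these patients back. The parallel rule for discontinuation could affect more patients, given the planned loss of up to 15%, but that does not make this rule sound.

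**Conclusion.** The point holds as a statement about the rule. Inadvertently unblinded patients are removed after randomisation and replaced. This can bias the comparison, and it does not fit the intention-to-treat analysis promised under Statistical methods. Neither the rate of unblinding nor its relation to arm is known.

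On the assumption of 15% exclusion in one arm only and a 10 to 20 point difference, the bias is 1.5 to 3.0 points and two-sided type I error is about 6.5% to 11%, in a direction that cannot be known in advance. Milder assumptions give almost nothing, and exclusion unrelated to arm and outcome gives none. Confidence is high that the rule exists and is unsound in principle, and low about how much it would matter in this trial. The plan's own sample size removes any power argument for keeping it.

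**What to change.** Under Randomization, group allocation, and blinding, delete the exclusion and replacement of unblinded patients. State instead that their outcomes continue to be collected at all visits, not only for safety, and that they are analysed in their allocated group in the primary intention-to-treat analysis. Add one sensitivity analysis that leaves them out, and report the number unblinded by arm from the documentation already required. State under Statistical methods that unblinding does not remove a patient from the intention-to-treat set. The parallel rule for patients who discontinue needs the same reconciliation.

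The cost is a few sentences in the protocol and one extra analysis, with no increase in sample size. The small downside is that some patient-reported scores in the primary analysis will come from patients who know their arm; the sensitivity analysis shows how much that matters.
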